### Dose Group

The starting dose is set at 1.2 mg/m², with dose escalation conducted according to the Modified Fibonacci Scheme, with escalation increments of 100%, 67%, 50%, 40%, 33%, and 33%. The dose escalation increments may be further adjusted based on the pharmacokinetic (PK), pharmacodynamic (PD), and safety data from the previous dose group.

If the maximum dose specified in this protocol (15 mg/m²) has not yet reached the maximum tolerated dose (MTD), the decision to continue dose escalation will be based on PK, PD metrics, and safety data. If PK or PD indicators suggest that the drug has not reached a saturating level of exposure in the body, the dose group will continue to escalate according to the Modified Fibonacci Scheme until MTD is observed or until sufficient drug exposure is achieved (the maximum drug exposure should not exceed the exposure levels observed at the dog HNSTD dose, which corresponds to an equivalent human dose of 36.88 mg/m²). The dose preceding the MTD may be considered the recommended dose for Phase II clinical trials.

Table 7 Dose Escalation Scheme

| **Group Number** | **1** | **2** | **3** | **4** | **5** | **6** | **7** | **…..** |
| --- | --- | --- | --- | --- | --- | --- | --- | --- |
| Escalation Ratio | Starting Dose | 100% | 67% | 50% | 40% | 33% | 33% | 33% |
| Administered Dose (mg/m^2^) | 1.2 | 2.4 | 4.0 | 6.0 | 8.4 | 11.2 | 15 | Previous Dose×33% increment  （Maximum Drug Exposure < 36.88 mg/m^2^） |
| Number of Cases | 3-6 | 3-6 | 3-6 | 3-6 | 3-6 | 3-6 | 3-6 | 3-6 |

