| **Number of subjects planned to be enrolled** | It is expected that 21 to 42 patients with relapsed or refractory B-cell-related hematologic malignancies will be enrolled, including but not limited to patients with B-cell lymphoma, multiple myeloma, B-cell acute leukemia, T-cell lymphoma, and T-cell acute leukemia who have experienced disease progression, relapse, or are unsuitable for standard treatment after receiving standard therapies. |
| **Trial groups and drug dosage** | This study will adopt a modified Fibonacci method for dose escalation, with seven predefined trial dose groups:   \| **Group** \| **1** \| **2** \| **3** \| **4** \| **5** \| **6** \| **7** \| **…..** \| \| --- \| --- \| --- \| --- \| --- \| --- \| --- \| --- \| --- \| \| Incremental ratio \| Initial dose \| 100% \| 67% \| 50% \| 40% \| 33% \| 33% \| 33% \| \| Dose (mg/m^2^) \| 1.2 \| 2.4 \| 4.0 \| 6.0 \| 8.4 \| 11.2 \| 15 \| Previous dose×33% increment  （Maximum drug exposure < 36.88 mg/m^2^） \| \| Number of subjects \| 3-6 \| 3-6 \| 3-6 \| 3-6 \| 3-6 \| 3-6 \| 3-6 \| 3-6 \|   If the maximum dose defined in this protocol (15 mg/m²) does not reach the MTD, the decision to continue dose escalation will be based on pharmacokinetic (PK), pharmacodynamic (PD) indicators, and safety data. If PK or PD indicators suggest that systemic drug exposure has not yet reached saturation, dose escalation will proceed according to the modified Fibonacci method until the MTD is observed or the drug reaches sufficient exposure in the body (the maximum drug exposure should not exceed the exposure at the canine HNSTD dose, which corresponds to an equivalent human dose of 36.88 mg/m²). |
| **Preparation and method of administration** | **Preparation Method:** The drug is prepared at room temperature. Before administration, each vial of PM (specification: 20 mg/vial) is reconstituted and diluted with sterile normal saline to an appropriate concentration until fully dissolved. After preparation, it must be administered via intravenous infusion over 30 minutes.  **Administration Method:** The drug is administered using an infusion pump through a peripheral vein, with an infusion volume of 50 mL and an infusion time of 30 minutes. The actual infusion time will be recorded. During the clinical trial, adjustments may be made to the drug concentration, infusion rate, infusion time, and infusion volume based on individual subject safety and tolerability. |

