| **Drug Administration Plan** | The dosing phase of this study includes three stages: the single-dose phase, the multiple-dose phase, and the extended dosing phase. The pharmacokinetics of the single-dose and multiple-dose administrations are combined, during which safety, tolerability, and preliminary efficacy are observed.  **1. Single-Dose Phase**  The single-dose escalation phase will begin with the starting dose and proceed in an ascending order from low to high doses, with 3 to 6 subjects enrolled in each dose group. In each dose group, 3 subjects will be enrolled sequentially, and a single dose will be administered on Day 1 (D1) at that dose, followed by a 6-day observation period (D2-D7). Each subject will receive treatment with a single dose.  **2. Multiple-Dose Phase**  After completing the pharmacokinetic blood sampling for the single-dose administration, if the subject is well-tolerated, they will enter the multiple-dose phase, with doses administered on Days 8, 11, and 15. Each subject will receive the same dose as in the single-dose phase, with the dose-limiting toxicity (DLT) observation period defined as the first administration to 25 days after the first dose. Initially, only one subject will be enrolled in each dose group to observe their tolerability and safety within the 25 days following the first dose. Only if this subject does not experience a DLT will the remaining two subjects in the same dose group be allowed to enroll simultaneously.  If none of the 3 subjects in a dose group experience DLT, the trial will proceed to the next dose group. If 1 out of the 3 subjects in a dose group experiences DLT, an additional 3 subjects will be recruited to receive the same dose of the investigational drug, and they will be monitored for DLT occurrence.  If 1 DLT occurs among the 6 subjects, the trial will proceed to the next dose group. If 2 or more DLTs occur among the 3 subjects, or if 2 or more DLTs occur among the 6 subjects, the trial will be reduced to the previous dose group. If the previous dose group has fewer than 6 evaluable subjects, an additional 3 subjects will be enrolled to bring the total number of evaluable subjects to 6. If no more than 1 DLT occurs among the 6 evaluable subjects, the trial will be halted, and that dose group will be declared as the maximum tolerated dose (MTD). If the previous dose group has already reached 6 evaluable subjects, the trial will be halted, and that dose will be declared as the MTD.  During the multiple-dose escalation trial, real-time analysis of the pharmacokinetic (PK) data for the selected dose groups will be conducted to determine whether the drug reaches a saturation state in the body based on PK and pharmacodynamic (PD) indicators.  **3. Extended Treatment Phase**  After completing the single-dose and multiple-dose phases, if the efficacy assessment indicates clinical benefit for the subject, they will enter the extended dosing phase. In the extended dosing phase, treatment may continue according to the original dosing regimen or with adjustments to the dose based on the subject's tolerability and existing clinical results. Each dosing cycle lasts 21 days, with doses administered on Days 1, 4, 8, and 11 of each cycle. The number of extended dosing cycles will vary based on the patient's efficacy; subjects who achieve an objective response rate of partial response (PR) or higher after 6 cycles may continue receiving the treatment until disease progression, while those who do not reach PR will discontinue the treatment. Efficacy and safety data will continue to be collected during the extended dosing phase. |

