| **MTD definition** | If no more than 1 case of dose-limiting toxicity (DLT) occurs among the 6 subjects within 25 days after the first dose, the highest dose that meets this condition will be defined as the maximum tolerated dose (MTD). If all planned dose groups have been completed and no DLTs are observed in the highest planned dose group, that dose will be considered the MTD. |
| **Statistical analysis** | The statistical analysis of this study will be conducted using SAS 9.4 (or a later version). The study results will be reported in the form of summary tables (or graphs) and listings, primarily using descriptive statistical methods. Numerical variables will be described using mean, standard deviation (SD), median (Med), first quartile (Q1), third quartile (Q3), minimum (Min), and maximum (Max). Categorical variables will be described using counts and percentages within each category.  The safety statistical analysis will include statistical assessments of the incidence of adverse events/adverse reactions, listings of adverse events, vital signs, laboratory tests, physical examination results, and electrocardiogram (ECG) findings.  Pharmacokinetic analysis will be conducted using the WinNonlin program with a standard non-compartmental model to calculate pharmacokinetic parameters of the drug, including T_max_, C_max_, AUC_0-t_, AUC_0-∞_, t_1/2_, MRT, CL, Ke, and V. Descriptive statistics will be used to report measurements such as mean, standard deviation, median, maximum, and minimum. In single-dose studies, an evaluation of the dose proportionality will be performed. In multiple-dose studies, the degree of drug accumulation will be assessed.  Efficacy evaluation analysis will include the assessment of PFS (progression-free survival), ORR (objective response rate), and DCR (disease control rate). |
| **Ethics-related information** | The PM human pharmacokinetic trial strictly adheres to the Declaration of Helsinki and the ethical guidelines for human medical research. The study protocol was implemented after being approved by the Medical Ethics Committee of West China Hospital, Sichuan University. |

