### Escalation Process

The trial begins with a low dose, enrolling 3-6 subjects in each dose group. The decision to proceed to the next dose group will be based on whether at least 3 evaluable subjects from the previous dose group experience Dose Limiting Toxicity (DLT) and the corresponding safety data within 25 days after the first administration. An evaluable subject is defined as one who has received ≥80% of the planned dose or has experienced DLT after at least one dose

The specific regulations for dose escalation are as follows:

Table 8 Dose Escalation Rules

| **Occurrence of DLT** | **Actions** |
| --- | --- |
| No DLT observed | Proceed to the next dose group |
| 1 DLT observed among 3 subjects | Recruit an additional 3 subjects to receive the same dose of the investigational drug and observe for DLT |
| 1 DLT observed among 6 subjects | Proceed to the next dose group |
| ≥2 DLTs observed among 3 or 6 subjects | Reduce to the previous dose group.   - If there are fewer than 6 evaluable subjects in the previous dose group, recruit an additional 3 subjects to reach a total of 6 evaluable subjects. If no more than 1 DLT is observed among the 6 evaluable subjects, terminate the trial, and that dose group will be considered the MTD. - If there are already 6 evaluable subjects in the previous dose group, terminate the trial, and that dose will be considered the MTD. |

**Enrollment Sequence for Subjects in the Same Dose Group:** At the beginning of each dose group, only 1 subject will be enrolled to observe the tolerability and safety of that subject within 25 days after the first administration.

- Only if this subject does not experience DLT can the remaining 2 subjects in the same dose group be enrolled simultaneously.
- If this subject experiences DLT, enrollment of the third subject can only occur after the second subject has completed the 25-day observation period following the first administration, and only if the second subject has not experienced DLT.

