## Definition of MTD

Within 25 days after the first dose, if ≤ 1 DLT occurs among 6 subjects, the highest dose that meets this criterion will be defined as the MTD. If all dose groups specified in the protocol have been completed and no DLT occurs in the highest dose group, then the highest dose will be determined as the MTD.

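### If the 15 mg/m² group ends with no DLT in three subjects, the protocol both declares 15 mg/m² the MTD and allows escalation on the ground that the MTD has not been reached

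*Protocol*

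**What the plan says.** Four parts of the protocol bear on what happens at 15 mg/m², the last numbered group in Table 7.

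- **MTD definition (section 3.5 and the synopsis row of that name).** The first sentence is a six-subject rule: "if ≤ 1 DLT occurs among 6 subjects, the highest dose that meets this criterion will be defined as the MTD". The second covers completion of the planned groups without toxicity at the top. In section 3.5, if "no DLT occurs in the highest dose group, then the highest dose will be determined as the MTD"; in the synopsis, if "no DLTs are observed in the highest planned dose group, that dose will be considered the MTD". The second sentence names no minimum number of subjects.
- **Dose groups (section 3.2.3 and the synopsis row on trial groups).** The synopsis describes a design "with seven predefined trial dose groups". Section 3.2.3 continues after the top one: "If the maximum dose specified in this protocol (15 mg/m²) has not yet reached the maximum tolerated dose (MTD"), PK, PD and safety data decide whether 33% steps go on, below a cap of 36.88 mg/m². The synopsis opens the same rule with "If the maximum dose defined in this protocol (15 mg/m²) does not reach the MTD".
- **Escalation rules (Table 8 in section 3.2.4 and the synopsis drug administration plan).** No DLT leads to the next group, and so does "1 DLT observed among 6 subjects". A dose is named the MTD only after at least 2 DLTs at the dose above, and on six evaluable subjects.
- **Phase II dose (end of section 3.2.3).** The dose below the MTD may be taken as the recommended Phase II dose. Nothing is said for the case where no MTD is reached.

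**The concern.** Finding the MTD is a primary objective, so its decision rule should give one answer for each result. For 0/3 at 15 mg/m² it gives two. Under section 3.5 the MTD is 15 mg/m², and the candidate Phase II dose in section 3.2.3 would be the one below it, 11.2 mg/m². Under section 3.2.3 the MTD may not have been reached, escalation may continue, and no Phase II candidate is named.

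The no-DLT sentence also relaxes the evidence. It allows a dose to be called maximum tolerated on three subjects with no higher dose tested. The other routes to an MTD, the first sentence of section 3.5 and de-escalation in Table 8, rest on six.

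**Working it through.** **Inputs.** Starting dose 1.2 mg/m², increments 100%, 67%, 50%, 40%, 33%, 33%, 3 to 6 subjects per group and the 36.88 mg/m² cap (Table 7); seven groups and 21 to 42 subjects (section 4.1); stopping rules (Table 8). The protocol states no DLT rate, so the rates below are assumptions.

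**Reproducing the plan's figures.** Applying the increments in turn gives 1.2, 2.4, 4.01, 6.01, 8.42, 11.19 and 14.89 mg/m², which agrees with the stated ladder ending at 15. Seven groups of 3 to 6 give 7 × 3 = 21 and 7 × 6 = 42. Both reproduce.

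**Which results can occur at 15 mg/m² on the way up.** Under Table 8 a group goes to six subjects only after 1/3. The reachable results are therefore 0/3, 1/6, 2/3, 3/3, 2/6, 3/6 and 4/6. Those with 2 or more DLTs lead to de-escalation. The rest compare as follows.

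| Result at 15 mg/m² | Section 3.5 and synopsis MTD definition | Section 3.2.3, synopsis dose text, Table 8 | Agreement |
|---|---|---|---|
| 0/3 | Second sentence: 15 mg/m² is the MTD | Proceed; MTD may not be reached; further steps possible | Conflict |
| 1/6 | Second sentence does not apply (a DLT occurred); first sentence names the highest dose with ≤ 1/6, which is settled only when escalation ends | Proceed; further steps possible | Ambiguous, but compatible |
| 0/6 | 15 mg/m² is the MTD | Arises only by filling the group after ≥ 2 DLTs at a higher dose; Table 8 then names 15 mg/m² the MTD | Agree |

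**How far apart the readings are.** The steps allowed after 15 mg/m² are 15 × 1.33 = 19.95, then 26.53, then 35.29 mg/m². The next, 46.94, exceeds 36.88. One reading stops at 15 mg/m²; the other can run to about 35 mg/m².

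**How often 0/3 occurs, given that 15 mg/m² is reached.** P(0/3) = (1 − p)³ for true DLT rate p:

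- p = 0.10: 0.9³ = 0.729
- p = 0.20: 0.8³ = 0.512
- p = 0.30: 0.7³ = 0.343
- p = 0.40: 0.6³ = 0.216

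**What 0/3 shows.** The exact one-sided 95% upper limit is 1 − 0.05^(1/3) = 0.632, so a true DLT rate of up to 63% is compatible with it.

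**The case against.** The best defence is that the second sentence of section 3.5 is a closing rule, used once the decision in section 3.2.3 is to go no further. Table 7 has an open column after group 7, with its own ratio, dose formula, cap and subject numbers, and section 4.1 calls seven groups provisional. On that view the specified groups are complete only when escalation ends, and the two rules follow one another. This reading is workable, and it is probably close to what was meant. But it is not stated. It fits poorly with a synopsis that ties the rule to the highest planned group and says "with seven predefined trial dose groups", and with 15 mg/m² being named as the protocol's maximum. Nor does it remove the labelling problem. Section 3.2.3 separates stopping because an MTD is seen from stopping because exposure is sufficient, whereas section 3.5 would call a DLT-free top dose the MTD in both cases.

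It is also fair to say that the Phase II sentence is permissive and binds nobody to 11.2 mg/m², and that neither reading skips the safety review before going higher.

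Four stronger readings are tempting and are not supported:

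- **Every non-toxic result at 15 mg/m² is contradictory.** The table above shows otherwise for 1/6 and 0/6. Adding the 1/6 route to the probability would overstate the conflict.
- **Table 8 declares the MTD not reached.** It says only to proceed to the next group.
- **The 36.88 mg/m² cap is wrong.** It is defined by exposure at the dog HNSTD and may rest on toxicokinetic data not shown. A body-surface conversion is a different measure and does not refute it.
- **The figure of 42 subjects is an error.** Section 3.1 only projects it, and Table 7 openly provides 3 to 6 subjects for each further group.

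**Conclusion.** The point holds for one result, 0/3 at 15 mg/m², and there the protocol is wrong as written: two rules for a primary objective give different answers and neither has precedence. If the trial reaches that dose, the result has a probability of 73% to 22% across assumed DLT rates of 10% to 40%, taking subjects as independent. These figures are conditional; the chance of reaching 15 mg/m² is not estimated. The same sentence lets the MTD rest on three subjects, against six elsewhere. For 1/6 the text is only unclear, and for 0/6 there is nothing to correct. The change should be made because the rule is central and the remedy is cheap. Whether to dose above 15 mg/m² remains a decision for the sponsor and the investigator.

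**What to change.** 1. In section 3.5 and the synopsis MTD definition, replace the second sentence with: *If the decision under section 3.2.3 is not to escalate beyond the highest dose tested, and no higher dose has had 2 or more DLTs, that group is filled to 6 evaluable subjects. If at most 1 of 6 has a DLT, the MTD is reported as not reached, with that dose given as the highest dose tested together with its DLT count. If 2 or more have a DLT, the row of Table 8 for 2 or more DLTs applies.*
2. In the same two places, limit the first sentence to the case where a higher dose was tested and had 2 or more DLTs. This also clears up the 1/6 case.
3. In section 3.2.3, reword the closing sentence on the Phase II dose so that a dose can be chosen when no MTD is reached.

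The cost is an amendment to these texts and at most three more subjects, if the last group stands at 0/3. No new procedure or sample is needed. Filling the group lowers the upper limit from 63% to 39% if the result is 0/6 (1 − 0.05^(1/6) = 0.393). With 1/6 it is 58% (95th percentile of a Beta(2, 5) distribution, 0.582), a small gain in precision, but on the same six-subject basis as the rest of the protocol.

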#### Chronic toxicity test in non-rodent Beagle dogs administered intravenously.

In this study, the low, medium, and high dose groups were set at 0.3, 1, and 3 mg/kg, respectively. The excipient was set at a high dose of 45 mg/kg. In the low dose group, occasional vomiting was observed; in the medium dose group, symptoms included vomiting, loose stools, and dark red stools; in the high dose group, symptoms included vomiting and dark red stools. Four dogs (4/10, 2 females and 2 males) died between days 13 and 26 of the experiment. Electrocardiogram (ECG) analysis showed that in the high dose group, male dogs exhibited increased heart rates and a slight prolongation of QTc (9.6%). Hematological analysis revealed that PLT, RET, and RET% were partially or fully reduced in the low, medium, and high dose groups, with an increase in APTT, indicating a dose-dependent relationship. Biochemical analysis showed that TP, TG, ALP, HDL, K+, and other parameters were partially or fully reduced in all dosing groups, also demonstrating a dose-dependent relationship. The primary toxic target organs or systems included the immune system (spleen, thymus, lymph nodes), digestive system (esophagus, liver, pancreas, intestine), kidneys, heart, lungs, trachea, testes, bone marrow, and injection site. There was a dose-dependent relationship, and recovery was observed during the recovery period. The highest no serious toxicity dose (HNSTD) was determined to be 1 mg/kg.

In conclusion, in the chronic toxicity study of injectable Purinostat Mesylate in dogs, the no observed adverse effect level (NOAEL) was found to be below 0.3 mg/kg, while the highest no serious toxicity dose (HNSTD) was 1 mg/kg.

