#### Pharmacokinetics in Non-Rodent Animals

**（1）Pharmacokinetics of Purinostat Mesylate After Intravenous Injection in Male and Female Beagle Dogs**

After a single intravenous injection of 0.3, 1, and 3 mg/kg Purinostat Mesylate in male and female Beagle dogs, the maximum blood concentrations (C_max_) were reached immediately after the injection, measuring 130 ± 35.5, 411 ± 162, and 1230 ± 166 ng/mL, respectively. The plasma clearance rates (CL) were 68.4 ± 13.2, 73.4 ± 17.9, and 71.5 ± 11.6 mL/min/kg, respectively. The steady-state apparent volume of distribution (Vdss) values were 3.69 ± 0.957, 3.85 ± 1.80, and 2.89 ± 0.605 L/kg, respectively. The elimination half-lives (T_1/2_) were 4.49 ± 0.669, 7.05 ± 3.07, and 8.47 ± 1.26 hours, respectively. The area under the plasma concentration-time curve from time zero to the last quantifiable time point (AUC_0-last_) was 75.1 ± 18.3, 238 ± 63.1, and 713 ± 122 h•ng/mL, respectively.

After a single intravenous injection of Purinostat Mesylate at doses of 0.3, 1, and 3 mg/kg in male and female Beagle dogs, the systemic exposure (AUC_0-last_ and C_max_) demonstrated a dose-dependent linear increase as the dose increased from 0.3 to 1 mg/kg and from 1 to 3 mg/kg. Overall, within the dose range of 0.3 to 3 mg/kg, the systemic exposure (AUC_0-last_ and C_max_) in both male and female animals showed a dose-dependent linear increase.

After the single intravenous administration in male and female Beagle dogs at doses of 0.3, 1, and 3 mg/kg, there were no significant gender differences in systemic exposure (AUC_0-last_ and C_max_). Following a continuous intravenous injection of 1 mg/kg Purinostat Mesylate once daily for 7 days, there was no significant accumulation observed on day 7 compared to day 1 for both male and female experimental animals.

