**（2）Plasma Protein Binding Rate**

The plasma protein binding rate of Purinostat Mesylate was measured using equilibrium dialysis in Sprague-Dawley rats, Beagle dogs, crab-eating monkeys, and human plasma. The experimental results indicated that at three tested concentrations (0.2, 2, and 10 µM), the binding rates (%) of Purinostat Mesylate were as follows: 94.3, 95.5, and 95.5 in Sprague-Dawley rat plasma; 83.1, 83.6, and 83.3 in Beagle dog plasma; 78.4, 79.5, and 79.0 in crab-eating monkey plasma; and 90.3, 90.0, and 90.4 in human plasma. At concentrations of 0.2, 2, and 10 µM, Purinostat Mesylate exhibited moderate binding rates in SD rat plasma (at the concentration of 0.2 µM), while demonstrating higher binding rates in SD rat plasma at the concentrations of 2 and 10 µM. The binding rates in the plasma of all four species did not show significant concentration dependence.

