**1）Estimation of the Maximum Recommended Starting Dose Based on Toxicology Results**

According to the "Guidelines for the Clinical Trial of Antineoplastic Drugs," for cytotoxic agents, the maximum recommended starting dose (MRSD) can be determined as one-tenth of the maximum tolerated dose (MTD) in rodent studies or one-sixth of the MTD in non-rodent species, expressed in mg/m². For some non-cytotoxic antineoplastic agents, due to their relatively lower toxicity, the starting dose for single administration in Phase I clinical trials can be calculated using one-fifth of the No Observed Adverse Effect Level (NOAEL) from non-rodent studies, or higher.

Based on the MTD calculations, the MRSD should be the value derived from the most sensitive species, which is 3.33 mg/m². From the NOAEL calculations, the MRSD should be less than 1.2 mg/m².

Table 2 Calculation of MRSD Based on MTD from Rodent and Non-Rodent Species

|  | MTD（mg/kg） | Km | HED（mg/m^2^） | MRSD（mg/m^2^） |
| --- | --- | --- | --- | --- |
| Rats | 30 | 6 | 180 | 18 |
| Beagle dogs | 1 | 20 | 20 | 3.33 |

*MTD: Maximum Tolerated Dose，Km: mg/kg Dose conversion to human equivalent dose inmg/m2 Dosing conversion factor，HED: Human Equivalent Dose，MRSD: Maximum Recommended Starting Dose*

Table 3 Calculation of MRSD Based on NOAEL from Non-Rodent Species

|  | NOAEL（mg/kg） | Km | HED（mg/m^2^） | MRSD（mg/m^2^） |
| --- | --- | --- | --- | --- |
| Beagle dogs | <0.3 | 20 | 6 | <1.2 |

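### The 36.88 mg/m² ceiling for dose groups added above 15 mg/m² is not derived and, on total drug, does not match the dog exposure limit that it is said to represent

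*Protocol*

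**What the plan says.** Section 3.2.3 plans seven groups up to 15 mg/m². If the MTD has not been reached there, further groups may follow in 33% steps after a review of PK, PD and safety. The stopping point is that maximum exposure "should not exceed the exposure levels observed at the dog HNSTD dose, which corresponds to an equivalent human dose of 36.88 mg/m²". The synopsis says the same: "should not exceed the exposure at the canine HNSTD dose, which corresponds to an equivalent human dose of 36.88 mg/m²". The last column of Table 7 shortens this to "Maximum Drug Exposure < 36.88 mg/m^2", and the synopsis table carries the same limit.

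The protocol also gives the quantities needed to test the figure:

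- Section 1.4.2.4, dog repeat-dose study: "the highest no serious toxicity dose (HNSTD) was 1 mg/kg".
- Section 3.2.1, Table 2, converts that dog dose by body surface (dose, Km, mg/m², starting dose): "Beagle dogs | 1 | 20 | 20 | 3.33".
- Section 1.4.3.2, dog single-dose AUC at 0.3, 1 and 3 mg/kg: "was 75.1 ± 18.3, 238 ± 63.1, and 713 ± 122 h•ng/mL, respectively".
- Section 3.2.1, Tables 5 and 6: six predicted human clearances, a formula linking dose to clearance and AUC, and a body surface of 1.65 m².

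**The concern.** One sentence sets two limits, an exposure and a dose, and presents them as equivalent. If they are not, the site has two different stopping points. The mg/m² figure is the easier one to apply, because the sentence and Table 7 give no AUC. If 36.88 is too high for the exposure it stands for, following it would open groups whose predicted AUC is above the dog level that the same sentence forbids.

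The dog data explain why that level was chosen. At the next dose tested, 3 mg/kg, 4 of 10 animals died (1.4.2.4), and the single-dose AUC at that dose was 713 ng·h/mL (1.4.3.2).

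**Working it through.** **Formula and check.** Section 3.2.1 gives Dose = CL × AUC × F / SF, with F = 1 for an infusion; dividing by 1.65 m² gives mg/m². It reproduces Table 6:

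- rat: 96.5 × 249 / 1000 / 10 / 1.65 = 1.46 mg/m² (stated 1.46)
- dog: 133.9 × 76 / 1000 / 10 / 1.65 = 0.62 mg/m² (stated 0.62)

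**Exposure-matched dose, total drug.** The ceiling equates exposures, so no safety factor applies (SF = 1). With the dog AUC of 238 ng·h/mL at 1 mg/kg, dose = CL × 0.238 / 1.65. Conversely, 36.88 mg/m² is 36.88 × 1.65 = 60.85 mg, so the predicted AUC is 60.85 × 1000 / CL.

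| Table 5 clearance (L/h) | Dose matching 238 (mg/m²) | AUC at 36.88 mg/m² (ng·h/mL) | Ratio to 238 | Dose matching on unbound drug (mg/m²) |
| --- | --- | --- | --- | --- |
| 74.64 | 10.8 | 815 | 3.4 | 17.7–18.8 |
| 96.5 | 13.9 | 631 | 2.6 | 22.8–24.3 |
| 100 | 14.4 | 609 | 2.6 | 23.7–25.1 |
| 106.7 | 15.4 | 570 | 2.4 | 25.2–26.8 |
| 133.9 | 19.3 | 454 | 1.9 | 31.7–33.7 |
| 164.16 | 23.7 | 371 | 1.6 | 38.8–41.3 |

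The clearance needed to make 36.88 correct is 60.85 / 0.238 = about 256 L/h, which is 1.56 times the highest in Table 5. With the dog AUC one SD higher (238 + 63.1 = 301.1), the largest matched dose is 164.16 × 0.3011 / 1.65 = 30.0 mg/m².

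**Body-surface comparison.** Table 2 gives 1 mg/kg × 20 = 20 mg/m², and 36.88 / 20 = 1.84. This converts a dose and does not match an exposure, so it is supporting evidence only.

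**Unbound drug (last column).** Section 1.4.3.2 reports binding of "83.1, 83.6, and 83.3 in Beagle dog plasma; 78.4, 79.5, and 79.0 in crab-eating monkey plasma; and 90.3, 90.0, and 90.4 in human plasma". The free fractions are 16.9, 16.4 and 16.7% in dogs and 9.7, 10.0 and 9.6% in humans, a ratio of 1.64 to 1.74. Multiplying the total-drug doses by that ratio gives 17.7 to 41.3 mg/m². This range contains 36.88 but does not yield it. At 36.88 mg/m² the unbound exposure is still above the dog value at five of the six clearances (1.1 to 2.1 times); only 164.16 L/h brings it below (0.89 to 0.95).

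**What the ceiling would admit.** Steps of 33% from 15 give 19.95, 26.5 and 35.3 mg/m², then 46.9. The figure of 36.88 therefore permits three added groups. On total drug, 26.5 and 35.3 exceed 238 at all six clearances and 19.95 exceeds it at five. At the lowest listed clearance, 35.3 mg/m² gives 35.3 × 1.65 × 1000 / 74.64 = about 780 ng·h/mL, above the 713 seen in dogs at 3 mg/kg; that is the worst listed case.

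**The case against.** The strongest reply is that an unexplained figure is not a contradicted one. The HNSTD comes from the repeat-dose toxicity study, whose AUC is not reported, whereas 238 is a single-dose value from the PK section. Table 5 holds predictions, and human PK existed when this version was written, since the sampling times were changed after the first patient (7.2.2). The binding data in the protocol widen the matched range until it includes 36.88. The clearance of 256 L/h is 71.0 mL/min/kg at the 60 kg assumed in 3.2.1, close to the measured dog values of 68.4 to 73.4, so the figure may come from dog clearance carried over unscaled. The operative clause already limits exposure. It applies only above 15 mg/m², after PK, PD and safety review, while the protocol expects the MTD within seven groups (3.1) and keeps one-patient lead-in enrolment and the DLT rules (3.2.4).

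Much of this stands. The mismatch is shown for total drug with predicted clearance, and nothing printed is a wrong calculation step. Two parts carry less weight. Accumulation is an unlikely source of an AUC 1.6 to 3.4 times higher, because after seven daily doses of 1 mg/kg "there was no significant accumulation observed on day 7 compared to day 1 for both male and female experimental animals", although that was not the toxicity study itself. An exposure clause with no AUC beside it, tied to a mg/m² figure, does not tell the site which limit governs.

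A reader might infer that 36.88 is a proven error, or that 20 mg/m² is the correct ceiling. The documents support neither. The inputs behind 36.88 are not shown, and 20 mg/m² is a body-surface conversion used for the starting dose.

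**Conclusion.** The point holds in a limited form. The ceiling of 36.88 mg/m² is not derived and is inconsistent with the inputs that the protocol states. On total drug, with the single-dose dog AUC of 238, the Table 5 clearances and 1.65 m², the matched dose is 10.8 to 23.7 mg/m², and 36.88 corresponds to 1.6 to 3.4 times the dog exposure. The result assumes proportional kinetics and would change if the sponsor used a binding correction, a higher dog toxicokinetic AUC or an observed human clearance, none of which the protocol states. Writing an exposure limit in dose units in the two tables is a plain labelling error.

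The effect is confined to contingent groups above 15 mg/m². A reader might infer that the planned groups rest on an unsafe ceiling, but the figure governs none of them. It still merits correction, because a limit of this kind acts before dosing, whereas the DLT rules act only after toxicity has appeared.

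**What to change.** For groups above 15 mg/m² only:

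1. State the governing limit as an AUC in ng·h/mL: the repeat-dose dog toxicokinetic AUC at 1 mg/kg, or 238 if that is the only value. Say whether it refers to total or unbound drug.
2. Before each added group opens, require the last cohort's observed AUC, projected to the next dose, to lie below that limit.
3. Correct the unit in the synopsis table and Table 7.
4. Remove 36.88 mg/m² unless its derivation (AUC, clearance, any binding correction) is given. If it is given, keep the figure only as an indicative dose subordinate to the AUC limit. Do not put 20 mg/m² in its place as a hard cap.

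The cost is amendment wording in the synopsis, 3.2.3 and Table 7, plus a check on PK that is already collected and, according to the synopsis, analysed in real time. The downside is that fewer added groups may be permitted. On total drug the predicted AUC at 15 mg/m² (24.75 mg) is 332, 256, 248, 232, 185 and 151 ng·h/mL across the six clearances from lowest to highest, so at the three lowest a limit of 238 is already passed and no group would be added. The choice between total and unbound drug therefore has to be made and justified openly.
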